## Abstract

**Background:**

Applying technology through the use of the Internet and mobile phones can help provide education and trained peer support for patients with diabetes after coronary artery bypass (CABG). We are conducting a randomized controlled trial to evaluate the efficacy and feasibility of mobile-based coaching intervention in improving risk-factor control and secondary prevention in patients with diabetes after CABG.

**Methods:**

The glycaemic control using miniprogram-based intervention in patients with diabetes undergoing coronary artery bypass to promote self-management (GUIDE ME) study is a multi-centre, randomized controlled trial of mobile intervention versus standard treatment with 6 months follow-up conducted in 2 hospitals in China. The interventions are education and a reminder system based on the WeChat mini-program. Participants in the intervention groups receive 180 videos (including lines) about secondary prevention education for 6 months as well as the standard treatment. Behavioural change techniques, such as prompting barrier identification, motivational skills, and goal setting, are employed. A total sample size of 820 patients would be adequate for the GUIDE ME study. The primary outcome is the change of glycaemic haemoglobin (HbA_1c_) at 6 months. Secondary outcomes include a change in the proportions of patients achieving HbA_1c_, fasting blood glucose, systolic blood pressure, low-density lipoprotein cholesterol (LDL-C) and medication adherence.

**Discussion:**

This trial is the first to investigate the efficacy of mobile phone WeChat-based video coaching and medication reminder mini-program system to improve self-management in patients with diabetes and coronary heart disease (CHD) after CABG and has the potential to be applied in resource-limited settings across diverse populations. If successful, such mobile intervention could be used and scaled up to improve care for this high-risk group of patients.

**Trial registration:**

ClinicalTrials, NCT04192409. Registered on December 10, 2019.

**Supplementary Information:**

The online version contains supplementary material available at 10.1186/s13063-023-07580-x.

## Background

Diabetes mellitus (DM) is associated with increased mortality and morbidity in patients undergoing coronary artery bypass grafting (CABG) specifically [1]. It is recommended that secondary prevention including long-term glucose control should ideally be optimized for this high-risk group of patients [1]. In low- and middle-income countries (LIMCs), including China, only one-third of individuals nationwide have adequate glycaemic control and over two-thirds of patients with coronary artery disease (CHD) take no medication [2, 3]. CABG patients with DM should receive coordinated medical care from a diabetes mellitus monitoring team. However, it is difficult to generalize and implement such interventions of patient-centred care given the limited access to education, consultation, and high costs of organization [4]. Given the high-risk profile of this subgroup among CHD patients, cost-effective and scalable interventions to enhance secondary prevention are urgently needed.

Applying technology through the use of the Internet and mobile phones can help provide education and trained peer support for patients after CABG, even for those who are unable to access cardiac rehabilitation because of geographic barriers [1]. As of August 2016, China had the largest number of mobile phone owners in the world. WeChat had become the most popular messaging communication app in China, which had a monthly-active-user of 549 million [5]. As such, WeChat has the potential to be a scalable and powerful tool to deliver health information.

There are thousands of mobile applications for supporting diabetes mellitus self-management, serving primarily as tracking and reference apps. In fact, < 1% of mobile applications have been evaluated through research and even fewer have demonstrated outcomes [6]. Prior studies showed inconsistent results. Evidence indicated that most trials to date have been designed to target a single condition and have not been based on behavioural change techniques (BCTs). Most of the studies were limited to single-centre studies and were underpowered [6, 7]. Thus, issues remain about the authentic role of mobile health. Most importantly, none of the studies specifically enrolled diabetic patients who had undergone CABG which are regarded as high-risk populations and usually manage multiple conditions, requiring several lifestyle and treatment recommendations [1].

Given the public health significance of poor diabetes management, high-risk profile in patients with concomitant diabetes after CABG and problems with previous studies, we design and conduct the glycaemic control using miniprogram-based intervention in patients with diabetes undergoing coronary artery bypass to promote self-management (GUIDE ME) study (NCT04192409).

The primary objective of this study is to evaluate the efficacy and feasibility of mobile-based coaching intervention, based on BCTs, in improving risk-factor control and secondary prevention in this high-risk group of patients.

## Methods

### Study overview

The ongoing GUIDEME study is a multi-centre randomized controlled trial of an automated mobile phone miniprogram-based intervention with 6 months of follow-up. We hypothesize that education and medication reminders for patients can help reduction of A1c over 6 months. This RCT is registered at http://www.clinicaltrials.gov (NCT04192409). The central ethics committee of Fuwai Hospital approved the study (No.2019–1151, June 2019). The recruitment and the last follow-up are expected to finish in June 2022 and December 2022, respectively. All participants provided written informed consent at the initial trial visit.

### Patient and public involvement

No patient was involved.

### Inclusion and exclusion criteria

Patients must meet all of the following criteria to be recruited for the study: (1) type 2 diabetes diagnosed by a physician prior to study enrollment; (2) documented coronary artery disease and isolated coronary artery bypass is recommended and performed; (3) access to a mobile phone with WeChat and ability to operate on the miniprogram. The participants are eligible if they are ≥ 18. Patients are excluded if they could not read the materials, had cognitive or communication disorders, and are unable to provide informed consent or die before discharge.

### Patient recruitment

We identify patients in the surgical ward who have been hospitalized with CHD and DM and who have undergone coronary artery bypass. The diagnoses of CHD and DM and the indication for surgical revascularization are adjudicated centrally, based on reviews of the patients’ medical charts. Once identified, study researchers explained the study face-to-face and that they may be eligible to participate. A ‘screening log’ of basic demographic information and reasons for not participating in patients deemed ineligible or declined to participate has been recorded. Individual patient signature informed consent is obtained by the China National for Cardiovascular Disease independent of clinical office involvement.

Based on previous experience [8], we estimate that surgical practice would provide an average of 1300 patients with CHD and DM undergoing CABG in Beijing Fuwai Hospital annually and 100 patients in Qingdao Fuwai Hospital.

### Allocation sequence generation

Participants are randomly allocated to enter the intervention or the control arm in a 1:1 ratio using a computerized randomization system using minimization. In order to achieve a balance of participants’ characteristics in both arms, a stratified randomization approach is employed, based on age, gender, education degree, acute myocardial infarction history and medical insurance type.

#### Allocation concealment mechanism

A computerized randomization system using the minimization method is developed to implement the allocation sequence.

#### Allocation implementation

A computerized randomization system using the minimization method will generate the allocation sequence. This allocation sequence will automatically assign participants into the intervention group or the control group. After this assignment, researchers will enrol participants and accomplish the assignment of participants to interventions.

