#### Blinding

Statisticians and clinic staff are blinded to treatment allocation.

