### Trial intervention

The interventions are education and reminder systems for patients with CHD and DM, using mobile phones to allow transmission (Fig. 1). Participants in the intervention groups receive video (including lines) about CHD and diabetes risk modification education for 6 months as well as the standard treatment. The control group receive standard treatment. The standard treatment included (1) short education lesson regarding the secondary prevention recommendations after CABG during hospitalizations. Antiplatelet therapy, antithrombotic therapy, lipid management, β-blocker therapy, hypertension management, and diabetes mellitus management are explained including what-, why- and how-. The recommendations are consistent with the 2015 AHA scientific statement—secondary prevention after coronary artery bypass graft surgery [1]. (2) A brochure. In this brochure, preoperative, postoperative and discharge education notifications are documented. With regard to discharge education notification, diet, physical activity, wound care, follow-up, and medication advice are documented. All patients in the intervention groups receive the study treatment mobile phone mini-program software which is anchored in WeChat (Fig. 2). A training session is held by the research staff on enrollment that participants in the intervention group are registered in the system so that they have access to the web-based individual patient portal and they are capable of receiving and reading system-driven coaching video material. In addition, participants in the intervention receive medication regimen reminders. Prior to commencement, the system is tested to confirm functioning effectively. Researchers at the China National for Cardiovascular Disease could monitor the visiting frequency of the system. Participants are also informed that they could withdraw from the study by sending text messages to the research staff. Outbound patient phone calls by the research staff are discouraged.

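### As written, researchers enrol patients after the system has assigned the arm, and the concealment section gives no safeguard against this

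*Protocol article*

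**What the plan says.** All references are to the protocol article.

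- **Allocation sequence generation:** patients are allocated "in a 1:1 ratio using a computerized randomization system using minimization".
- **Allocation concealment mechanism:** the whole section is one sentence: "A computerized randomization system using the minimization method is developed to implement the allocation sequence".
- **Allocation implementation:** the system generates the sequence, and "This allocation sequence will automatically assign participants into the intervention group or the control group". The next sentence reads: "After this assignment, researchers will enrol participants and accomplish the assignment of participants to interventions".
- **Blinding:** "Statisticians and clinic staff are blinded to treatment allocation". Enrolling researchers are not mentioned.
- **Patient recruitment:** "Once identified, study researchers explained the study face-to-face and that they may be eligible to participate". The section also provides for central adjudication of the diagnoses and the surgical indication, consent taken independently of the clinical office, and a screening log.
- **Study overview:** "All participants provided written informed consent at the initial trial visit". The visit is not placed before or after randomisation.
- **Trial intervention:** "A training session is held by the research staff on enrollment that participants in the intervention group are registered in the system".

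**The concern.** Concealment means that whoever decides on a patient's entry cannot know the arm until that decision is final. The Allocation implementation section states the reverse order, with assignment first and enrolment second, and has the same researchers enrol patients and put the assignment into effect. On that order a patient could be enrolled, delayed or left out in the knowledge of the arm.

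If that happened, the arms could differ from the start in motivation or capacity for self-management, both plausibly related to the change in HbA1c, which is the primary outcome. An intention-to-treat analysis protects the comparison only if its denominator is everyone assigned. If the denominator is those enrolled after assignment, the selection is already inside the analysis set, and covariate adjustment cannot be relied on to remove it.

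**Working it through.** No arithmetic bears on this point, so the check sets the sections side by side.

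1. **Is the order really stated?** Yes. In Allocation implementation, the assignment that comes before enrolment is the automatic one described in the sentence just before it. The text affirms a procedure; it is not a detail that a condensed article has left out.

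2. **Does the concealment section correct it?** No. Minimisation is a method for choosing the arm. Naming it does not say when the arm becomes visible or to whom. Nothing in the section says that eligibility and consent are closed before the system answers.

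3. **Does the blinding section correct it?** No. It covers statisticians and clinic staff. The researchers who approach and enrol patients are not listed.

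4. **Do the consent statements correct it?** No. Study overview puts consent at the initial trial visit, but does not place that visit relative to randomisation. Patient recruitment separates consent from the clinical office, which is not the same as separating it from knowledge of the arm.

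5. **Does the intervention section help?** It neither reverses the order nor proves it. Arm-specific training at enrolment fits the arm being known by then. It would also fit a patient who was fully registered, then allocated, then trained on the same day.

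6. **Does the order matter under these entry criteria?** Yes. Ability to operate the mini-program is required of every patient in both arms. It calls for judgement, as does the exclusion for cognitive or communication disorders. Such criteria are harmless when settled before the arm is known, but can be applied differently by arm when settled afterwards.

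No section reverses the stated order, and none says that the arm is withheld until registration.

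**The case against.** The strongest reply is that the sentence is clumsy and does not describe practice. Minimisation on age, gender, education, infarction history and insurance type cannot run until those facts are known for the patient. The patient must therefore already have been identified, and probably interviewed. The article calls those being allocated participants, and says that all participants consented. The sentence may simply run together three functions (generating the sequence, enrolling and assigning), or may use enrolment for entering an already consented patient into an arm. Central adjudication, independent consent, the screening log and monitoring of recruitment also limit discretion and would help to expose selective entry.

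Much of this stands. It makes loose wording a live possibility, and the controls are real. But entering baseline factors is not irrevocable registration, and none of the controls places eligibility and consent before the arm is revealed.

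A reader might infer more than the article supports:

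- **That concealment failed.** The article describes a plan and gives no evidence of what happened.
- **That minimisation makes the next allocation predictable.** The article does not say whether the algorithm has a random element, and does say that allocation is random. That detail may stand in the full protocol, so no change to the algorithm follows.
- **That the mini-program requirement falls on one arm.** It is an inclusion criterion for all patients.
- **That there is wide scope for biased selection because only some candidates are recruited.** A target of 820 set against the expected yearly caseload of 1,300 + 100 = 1,400 reflects eligibility, refusal and the planned size. Selection before allocation affects generalisability, not balance between arms.

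**Conclusion.** The stated procedure is wrong as written. It puts enrolment after assignment, and the section that should explain concealment does not do so. If the text is followed literally, allocation is not concealed and selective enrolment by arm is possible.

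No size can be given. That would need the number allocated but not enrolled in each arm and how their HbA1c change would have differed, and the article gives neither. A bias figure built on assumed values for both would show nothing about this trial.

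The conclusion rests on the plain meaning of the Allocation implementation section and on the absence of any correcting statement elsewhere in the article. Because the wording may be loose, this is an important correction, but not one on which the trial stands or falls. It would become critical if system logs showed that allocation did precede registration.

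**What to change.** **Text.** Reconcile Patient recruitment, Allocation concealment mechanism, Allocation implementation and Trial intervention to one order:

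1. eligibility confirmed;
2. consent obtained;
3. baseline minimisation factors entered and locked;
4. patient irrevocably registered;
5. arm revealed, and only then the arm-specific training.

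State that the intention-to-treat set is everyone who received an assignment.

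**Patients already randomised.** Recruitment began in January 2020 and was expected to end about June 2022, so rewording alone does not settle what was done. Compare the system's timestamps for consent, registration and allocation. Report by arm the number allocated but not enrolled, with reasons. If every registration precedes its allocation, say so, and the point is closed.

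**Cost.** The rewording costs almost nothing if the system already works in this order. The timestamp check is one extract from the randomisation system and the consent records. Sample size, outcomes and the allocation algorithm stay as they are.

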#### Blinding

Statisticians and clinic staff are blinded to treatment allocation.

### Trial intervention

The interventions are education and reminder systems for patients with CHD and DM, using mobile phones to allow transmission (Fig. 1). Participants in the intervention groups receive video (including lines) about CHD and diabetes risk modification education for 6 months as well as the standard treatment. The control group receive standard treatment. The standard treatment included (1) short education lesson regarding the secondary prevention recommendations after CABG during hospitalizations. Antiplatelet therapy, antithrombotic therapy, lipid management, β-blocker therapy, hypertension management, and diabetes mellitus management are explained including what-, why- and how-. The recommendations are consistent with the 2015 AHA scientific statement—secondary prevention after coronary artery bypass graft surgery [1]. (2) A brochure. In this brochure, preoperative, postoperative and discharge education notifications are documented. With regard to discharge education notification, diet, physical activity, wound care, follow-up, and medication advice are documented. All patients in the intervention groups receive the study treatment mobile phone mini-program software which is anchored in WeChat (Fig. 2). A training session is held by the research staff on enrollment that participants in the intervention group are registered in the system so that they have access to the web-based individual patient portal and they are capable of receiving and reading system-driven coaching video material. In addition, participants in the intervention receive medication regimen reminders. Prior to commencement, the system is tested to confirm functioning effectively. Researchers at the China National for Cardiovascular Disease could monitor the visiting frequency of the system. Participants are also informed that they could withdraw from the study by sending text messages to the research staff. Outbound patient phone calls by the research staff are discouraged.

**Fig. 1 Fig1:**
[figure not shown]
Schematic to show patient mobile connection, patient/physician web portals and servers

**Fig. 2 Fig2:**
[figure not shown]
Functional modules of coaching and reminder on the WeChat terminal

### Intervention development

A cluster of 180 videos are developed by a multidisciplinary team of cardiac surgeons, cardiologists, endocrinologists, psychologists, nurses and public health researchers using a two-phase systemic and iterative approach. Coaching videos cover a range of secondary prevention after coronary artery bypass graft surgery in addition to diabetes self-management topics based on current guidelines [1, 9–13] including (1) general education on CHD and DM, (2) postoperative antiplatelet agents; (3) lipid-lowering therapy; (4) b-blocker therapy; (5) glucose monitoring and control, (6) blood pressure control, (7) smoking cessation; (8) cardiac rehabilitation; and (9) lifestyle recommendations such as weight loss, physical activity, diet. Other self-care behaviours including monitoring, self-management problem solving, reducing risks and healthy coping are considered as essential bahaviours for improving diabetes mellitus self-management and are incorporated into video development accordingly [14, 15]. All videos are in Chinese and are less than 2 min. The captions of the videos are affiliated and are also developed into text.

### Phase I: developing videos

Lines of the coaching videos are originally drafted in Chinese based on current guidelines. BCTs are employed to develop short videos including goal setting, providing information on consequences of behaviour, self-monitoring, barrier identification and social support [16, 17]. Table 1 illustrates the BCTs used in the lines of short videos. Videos were developed in form of lectures or dialogues in order to make them more acceptable to patients and compatible with Chinese beliefs and values [18]. Lectures begin with a question regarding to the subject and are followed by the response. Videos of dialogue are made in the setting of real-world examples instead of abstract theories [19]. These videos are sent to experts in BCTs and subsequently reviewed, criticized and revised within the research team.

**Table 1 Tab1:** Behaviour change technique used in video development

Behaviour change technique	Content/explanation	Examples of lines of video in English
Provide information about behaviour-health risk	General information about behavioural risk	Aspirin should be continued indefinitely to reduce graft occlusion and adverse cardiac events. In order to convey the most benefit of CABG to you, taking medications regularly
Provide instruction	Tell the person how to perform a behaviour and/or preparatory behaviours	Smoking cessation is critical. Electronic cigarettes (e-cigarettes) have not been demonstrated to improve cessation rates and important concerns have been raised about their potential for adverse health effects. However, nicotine replacement therapy, such as bupropion and varenicline as adjuncts to smoking cessation for stable CABG patients after discharge is reasonable. And you can try this method!
Prompt barrier identification	Identify barriers to perform the behaviour and plan ways of overcoming them	b-Blockers are often associated with side effects such as weight gain, fatigue, and sexual dysfunction. You may feel upset about this and are reluctant to take it regularly. But if you have hypertention, a history of myocardial infarction or a history of heart failure, keep taking it regularly as this is good for your body. We will remind you to take this medication through miniprogram. And you can also set a repeating alarm on your cellphone
Prompt self-monitoring of behaviour	The person is asked to keep a record of the specified behaviour	Meals, exercise, cold and diarrhoea will make your blood sugar levels fluctuate. Thus, you should perform self-monitoring of blood glucose (SMBG) prior to meals and snacks, at bedtime, occasionally postprandially, prior to exercise and prior to critical tasks such as driving. You may as well upload this data through the mini-program. In addition, perform the A1C test 3 months and 6 months after surgery even if you have stable glycaemic control. Striving to achieve an HbA_1c_ is a reasonable goal for most patients after CABG
Set graded tasks	Set easy tasks, and increase the difficulty until target behaviour is reached	Have you ever felt hard to take medicine regularly? All things are difficult before they are easy. However, our mini-program system will help you. You can enter your medication and the system will automatically generate the ratings according to your medication adherence performance. More stars you get, the more benefits you will gain. Move on to get the most stars and it will make a great difference in the future!
Plan social support or social change	Prompt consideration of how others could change their behaviour to offer the person help or (instrumental) social support	Symptoms of hypoglycaemia include, but are not limited to shakiness, irritability, confusion, tachycardia, and hunger. Tell your friends and family when you have the symptoms above so that they give you the glucose (15–20 g). Fifteen minutes after treatment, if SMBG shows continued hypoglycaemia, the treatment should be repeated. Once SMBG returns to normal, the individual should consume a meal or snack. The family members should know where the glucagon is and how to administer it in case of blood glucose < 54 mg/dL
Stress management	May involve a variety of specific techniques (eg. Progressive relaxation) that do not target the behaviour but seek to reduce anxiety and stress	Relaxation is something we need to learn and practice. Listening to music, reading or talking to friends and family can ease stress
Motivational interviewing	Prompt the person to provide self-motivating statements and evaluations of their own behaviours to minimize resistance to change	Does your A1C decrease in value 3 months after CABG? If so, it is something worth celebrating. We are sure that you have put a lot of effort into taking medications and lifestyle modification. Keep up the good work and you can make a difference. If A1C remains less than 7%, it is supposed that you achieve the target of glycaemic control. However, less stringent A1C goals (such as < 8%) may be appropriate according to recent guidelines. Thus, glycaemic target must be individualized to the needs of each patient and his or her disease factor

